In the present randomized clinical trial (RCT) we will compare the effects of VF-based balance training on standing balance performance in patients with PD with the effects of conventional balance training. In addition, we will investigate to what degree the improvements in standing balance are accompanied by changes in cortical activity. To this end, we will employ whole-head electroencephalographic (EEG) recordings during a postural task [19,20].

We hypothesize that VF-based training is more effective than usual training in improving standing balance performance, with functional reach distance as the primary outcome. We also hypothesize that VF-related changes in balance performance are associated with more pronounced (movement-related changes in) beta synchronization in primary motor areas [21-23] and corresponding changes in functional connectivity of the entire motor network (including, e.g., pre-motor and supplementary motor areas), which may reflect the learning of novel strategies to control standing balance.

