## Methods

### Design and procedures

This study is a pilot RCT comparing two treatment groups of patients with PD (Figure 1). Patients are allocated to either a five-week training program with balance exercises containing augmented VF (experimental group), or a five-week balance training program that follows existing guidelines (control group). Assessments will take place before intervention (T0), at six weeks (T1), and at twelve weeks (T2). Intervention assignment will be concealed by drawing opaque sealed envelopes by an independent investigator not involved in the study. A blinded researcher will perform the assessments. Patients will be asked to refrain from mentioning the nature of the intervention they receive to the researcher. All assessments will be performed in the ON-phase of levodopa medication. To minimize the effects of (changes in) PD medications on the patients’ physical performance, the time of day at which patients are assessed will be kept constant throughout the study.

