#### Primary outcome measure

The Functional Reach Test (FRT) is used as primary outcome measure. The FRT measures the anterior limits of stability as perceived by the subject by assessing the maximal forward reaching distance. This outcome can be classified on the level of *activities* within the international classification of functioning, disability and health [25]. Lim and colleagues reported a mean score of 33.5 ± 7.4 cm in 26 patients with PD (range 22-50 cm) [14]. We note that for patients with PD the minimal detectable change is estimated to be between 9 [26] and 11.5 cm (smallest detectable difference) [27]. The test shows moderate inter- and intra-observer reliability [27,28].

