### Sample size calculation

We calculated the sample size required to obtain sufficient power for finding a difference of 9 cm on the FRT. Pooled estimate of the common variance, calculated from data by Ashburn [44], was entered in a formula for two independent groups with paired observations [45]. A total sample size of twenty-four patients is necessary to find a difference between groups with at least 80% power. To account for smaller effect sizes and an estimated attrition rate of 10%, we plan to include thirty-six patients in total, eighteen in each group.

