### Statistical analysis

Group differences in baseline patient characteristics will be tested using χ^2^-tests for categorical data and *t*-tests for continuous variables. Continuous outcome measures that are measured at all three time points will be tested for normality using the Shapiro-Wilk test. If assumptions for parametric testing are met, a mixed design ANOVA with between-subjects factor *group* (experimental vs. control) and within-subjects factor *time* (T0, T1, and T2) will be used to analyze the differential effect of the two interventions and the effect of time. If normality is rejected, or if outcomes are measured on the ordinal level, change scores between T1 – T0 and between T2 – T1 will be subjected to nonparametric Mann–Whitney U-tests. P < 0.05 will be set (two-tailed) as threshold for significance. Relative phase will be assessed through circular statistics using, in particular, Rayleigh tests to analyze group differences of relative phase uniformity between sources [46]. Correlation coefficients will be compared to investigate the association between outcomes.

Statistical analyses regarding EEG outcomes will be conducted using the methods outlined by Houweling and co-workers [47], with adaptations to EEG data regarding the accompanying lead field. Sources will be determined via pseudo *z*-scores of the beamformers that will be tested for within-group consistency through permutation tests [48]. The (relative) phases of the source projected EEG activity in the beta frequency band will be assessed through circular statistics (see above).

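### The functional reach analysis treats baseline as an outcome level and ties no contrast or visit to the primary hypothesis; a baseline-adjusted T1 comparison would be a cheap improvement

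*Protocol article*

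**What the plan says.** The Background of the protocol article states a directional hypothesis: "We hypothesize that VF-based training is more effective than usual training in improving standing balance performance, with functional reach distance as the primary outcome". The Primary outcome measure section repeats that "The Functional Reach Test (FRT) is used as primary outcome measure". Neither names the visit at which superiority is to be judged, although the FRT is assessed before training (T0), at six weeks (T1) and at twelve weeks (T2).

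The Statistical analysis section has no separate rule for the primary outcome. The FRT falls under the general rule for continuous outcomes measured at all three visits. If parametric assumptions are met, a mixed ANOVA with between-subject factor group and within-subject factor time (T0, T1, T2) "will be used to analyze the differential effect of the two interventions and the effect of time". If normality is rejected, "change scores between T1 – T0 and between T2 – T1 will be subjected to nonparametric Mann–Whitney U-tests". The threshold is 0.05, two-tailed.

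The Sample size calculation section targets 9 cm on the FRT. A pooled variance, whose value is not given, "was entered in a formula for two independent groups with paired observations". This yields 24 patients for at least 80% power, raised to 36 to allow for smaller effects and 10% attrition.

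**The concern.** A superiority claim on one outcome needs one comparison that answers it: which arm, at which visit, by how many centimetres. The ANOVA as described does not single one out.

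- The interaction asks whether the between-arm difference is the same at all three visits. A significant result says that the arms' profiles differ, but not which arm is better, when, or by how much. That has to come from follow-up contrasts, which the article does not name.
- The group main effect, if anyone used it, averages in T0, where randomised arms differ only by chance.
- T0 is measured in every patient but is not used as a covariate, which would usually sharpen the comparison.
- The fallback asks a different question. It replaces the omnibus test with two change-score tests. The second (T2 − T1) looks only at change between the two follow-up visits, and T2 − T0 is not compared at all. What is tested on the primary outcome therefore depends on a Shapiro-Wilk result.

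At stake are the clarity of the primary result and, in some scenarios, power. The validity of the 5% level is not at stake.

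**Working it through.** **Inputs.**
- From Sample size calculation: 9 cm, 24 patients, at least 80% power, 10% attrition, 36 planned. Evaluable: 36 × 0.9 = 32.4, taken as 16 per arm.
- SD σ = 7.4 cm, from Primary outcome measure. It is the only FRT SD in the document. It is cross-sectional and is not stated to be the variance used for sizing.
- Visit correlation ρ: the same section gives a minimal detectable change of 9 to 11.5 cm. If that is 1.96 × √2 × SEM, then SEM = 11.5/2.772 = 4.15 and ρ = 1 − (4.15/7.4)² = 0.69; or SEM = 9/2.772 = 3.25 and ρ = 0.81. I added 0.5 as a low value.
- True difference 5 cm: my assumption. The document allows for smaller effects but gives no figure.
- Equal variances and correlations across visits (compound symmetry).

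**The plan's own figure.** The variance is not given, so 24 cannot be reproduced. With 12 per arm and SD 7.4 for the analysed quantity, the noncentrality is 9/(7.4 × √(2/12)) = 2.98 on 22 df, and power is 81%. Power stays at 80% up to an SD of about 7.5 cm. So 24 is plausible but not verifiable.

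**Group main effect.** It estimates (0 + d1 + d2)/3. A sustained difference D appears as 2D/3 and a T1-only difference as D/3. The variance of a patient's three-visit mean is σ²(1 + 2ρ)/3. Power for a sustained 5 cm at ρ = 0.69 is 28%; for a sustained 9 cm it is 70% (78% at ρ = 0.5, 66% at ρ = 0.81).

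**Group by time interaction.** λ = (n/2) × Σ(dj − d̄)² / [σ²(1 − ρ)], with 2 and 60 df.
- Sustained (0, 5, 5): the sum of squares is 16.67, so λ = 8 × 16.67/(54.76 × 0.31) = 7.85 and power is 69%.
- T1 only (0, 5, 0) and T2 only (0, 0, 5): the sum of squares is again 16.67, so power is again 69%. The test does not distinguish these three patterns.
- Half lost by T2 (0, 5, 2.5): the sum of squares is 12.5, λ = 5.89 and power is 55%.

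**Baseline-adjusted comparisons** (29 df).
- ANCOVA at T1: residual variance σ²(1 − ρ²) = 28.7; noncentrality 5/√(2 × 28.7/16) = 2.64; power 72%.
- ANCOVA of the T1/T2 mean, sustained effect: residual variance σ²(1 − ρ)(1 + 2ρ)/2 = 20.2; noncentrality 5/√(2 × 20.2/16) = 3.15; power 86%.

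Power at 5 cm, ρ = 0.69, with values at ρ = 0.5 and 0.81 in brackets:

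| Pattern | Group × time | ANCOVA at T1 | ANCOVA of T1/T2 mean |
|---|---|---|---|
| Sustained | 69% (47 to 89) | 72% (57 to 88) | 86% (74 to 96) |
| Half lost by T2 | 55% (37 to 78) | 72% (57 to 88) | 63% (50 to 79) |
| T1 only | 69% (47 to 89) | 72% (57 to 88) | 33% (26 to 46) |
| T2 only | 69% (47 to 89) | 5% | 33% (26 to 46) |

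**At the 9 cm design effect.** For a sustained effect, the interaction has 94% power at ρ = 0.5 and more than 99% at 0.69 and 0.81; ANCOVA at T1 has 97% at ρ = 0.5 and more than 99% otherwise. If half is lost by T2, the interaction has 86% at ρ = 0.5 against 97% for ANCOVA at T1, the widest gap. At ρ = 0.69 it has 97.5% against 99.6%.

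**Simulation check** (20,000 trials, ρ = 0.7). With no effect, the interaction rejects in 4.8% of trials and the group main effect in 5.2%. With a sustained 5 cm, the interaction has 70% power and ANCOVA at T1 71%; the formulas give 70% and 73.5%. The ANCOVA formula ignores the small cost of chance baseline imbalance, so it is about 2 points optimistic.

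**The case against.** The strongest reply is that the planned analysis is valid and that the article signals which term it means. Randomised arms have equal expected T0 means. An equal between-arm difference at all three visits is therefore the same as no treatment effect at T1 or T2. The wording about a differential effect most naturally points to the interaction. This stands, and three stronger readings fail.

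- A reader might infer that neither group-related F-test addresses the hypothesis. The interaction does, at its nominal level. Being non-directional is no fault in itself where two-tailed testing is specified.
- A reader might infer that the false-positive rate is about double 5%. In simulation the chance that at least one of the two group-related F-tests is significant under the null is 9.7%. But the plan never names the group main effect as a test of efficacy, so this rule is not the plan's. The dilution to 2D/3 likewise matters only if that term is used.
- A reader might infer that the trial was sized for an unrelated analysis. The formula lies in a cited source that is not shown. With two visits, comparing paired changes between two groups is the group by time interaction, so the two belong to the same family. All that can be said is that a three-visit 2-df test is not obviously what was sized.

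The reply is also right that the power gain from a T1 test is modest. It is about 3 points for a sustained 5 cm effect, or about 1 by simulation, and nil at correlation 0.81. A benefit that appears only at T2 would be missed by a T1 test and detected by the interaction. Finally, this is a condensed article on a pilot trial, and an analysis plan that is not shown may name the contrast. That lowers the severity. It does not remove the point, because the article does state a superiority hypothesis, a powered sample size and a specific model.

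**Conclusion.** The point holds as a cheap improvement, not as an error that must be corrected before the trial can be interpreted. The stated model uses T0 as an outcome level and ties no contrast or visit to the FRT hypothesis. Its interaction is a valid but omnibus test that yields no signed estimate in cm.

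At an assumed 5 cm, the interaction falls short of ANCOVA at T1 by 17 points (55% against 72%) if half the effect is lost by T2. For a sustained effect it falls short of a baseline-adjusted T1/T2 mean by 17 points (69% against 86%), and it is close to ANCOVA at T1. It is better than ANCOVA at T1 when benefit appears only at T2, and better than the adjusted mean when benefit is confined to one visit.

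These figures rest on SD 7.4 cm, 16 per arm, correlation 0.5 to 0.81, compound symmetry and an effect size that the document does not give.

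**What to change.** In Statistical analysis, add a primary-analysis statement for the FRT: the between-arm difference at T1, adjusted for T0 FRT, reported in cm with a 95% CI and tested two-sided at 0.05. Estimate it by ANCOVA, or by a mixed model with T1 and T2 as outcomes and T0 as covariate. Report the T2 difference (retention) as secondary from the same model. The non-normality fallback should address the same T1 contrast, so that the question does not depend on a normality test.

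The cost is one paragraph, with no new data, visits or patients. The real price is that a T1 primary test has no power, beyond its 5% level, for a benefit that emerges only at T2. If the investigators consider that pattern likely, they should settle the primary visit with that in mind before any outcome data are seen.

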#### Secondary outcome measures

To explore other effects related to training with augmented VF, secondary outcome measures related to balance and gait, the patients’ health status and their level of activity and participation, as well as measures derived from posturographic and EEG measurements will be assessed.

a) *Measures of balance and gait*: the Berg Balance scale assesses how well each of fourteen different balance-related tasks is executed [29]. The timed single leg test is a measure of how long the subject can maintain balance while standing on one leg [30]. The 10 m Walk Test will be used to record walking capacity at comfortable walking speed [26].

b) *Measures of patients’ health status and level of activity and participation*: parts I, II, III and IV of the Unified Parkinson Disease Rating Scale (UPDRS) will be assessed to evaluate disease severity and disease-specific impairments [31]. Items 13–15 and 29–30 of the UPDRS will be used to compute the posture and gait score subscore [15]. The Falls Efficacy Scale consists of ten questions related to the patient’s confidence not to fall during a number of everyday tasks [9,32]. The Parkinson’s Disease Questionnaire (PDQ-39) is a comprehensive questionnaire that provides a measure of health status along eight dimensions [33]. The Hospital Anxiety and Depression Scale addresses feelings of anxiety and depression related to being physically ill [34]. The Multidimensional Fatigue Inventory is a questionnaire developed to obtain insight into the level of fatigue [35].

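### Ordinal scales are subtracted before ranking: Mann-Whitney on change keeps its type I error, but it depends on scale spacing and is usually less efficient than a baseline-adjusted rank analysis

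*Protocol article*

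**What the plan says.** The Statistical analysis section of the protocol article sets two routes. Continuous outcomes that pass a Shapiro-Wilk test go to a mixed-design ANOVA. For the rest: "If normality is rejected, or if outcomes are measured on the ordinal level, change scores between" T1 and T0 and between T2 and T1 "will be subjected to nonparametric Mann–Whitney U-tests". The threshold is fixed for all tests: "P < 0.05 will be set (two-tailed) as threshold for significance". No adjustment for the baseline value is stated on the ordinal route.

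The section does not list which outcomes count as ordinal. Candidates appear under Secondary outcome measures. One is a sum of rated tasks: "the Berg Balance scale assesses how well each of fourteen different balance-related tasks is executed". The UPDRS parts, a UPDRS posture and gait subscore, the Falls Efficacy Scale and several questionnaires are others. No baseline distribution, pre-post correlation or share of patients at a scale limit is given for any of them.

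**The concern.** An outcome takes this route because its steps cannot be assumed equal, yet the first operation applied to it is a subtraction, which is meaningful only if they are. Three consequences follow.

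- **Spacing.** The ranks of the differences depend on how the scale is numbered, so the p-value uses more than the ordering of the scores.
- **Scale limits.** A patient at the best score at both visits has change zero, the same as a patient lower down who did not respond.
- **Efficiency.** The baseline value is used by subtraction with a fixed coefficient of one instead of by adjustment, which usually costs power.

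At stake is how well a small trial can detect an arm difference on the rating scales that supplement the primary outcome. The problem is separate from the choice of visits to subtract: any pair has it.

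**Working it through.** **The plan's own figure.** The protocol gives no power figure for the ordinal outcomes. Its one calculation concerns the primary outcome, for "finding a difference of 9 cm on the FRT": "A total sample size of twenty-four patients is necessary to find a difference between groups with at least 80% power". The SD is not printed, only its origin ("Pooled estimate of the common variance, calculated from data by" a cited study). The only printed SD comes from another source: "mean score of 33.5 ± 7.4 cm in 26 patients with PD". With that SD, n per arm = 2 × (1.960 + 0.842)² × 7.4² / 9² = 10.6, so 11, or 22 in total. By the t distribution, 12 per arm has 81% power. So 24 is plausible, and nothing below depends on it.

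**Step 1: spacing (no assumptions).** Patient A goes from 30 to 34 and patient B from 50 to 53. The changes are +4 and +3, so A ranks above B. Squaring the scores leaves every ordering on the scale intact. The changes become 34² − 30² = 256 and 53² − 50² = 309, so B ranks above A. The input to Mann-Whitney has changed although no ordinal information has.

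**Step 2: scale limits (no assumptions).** Maximum at T0 and maximum at T1 gives 0. A mid-scale score that does not move also gives 0. The two are tied.

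**Step 3: power (simulation, assumed inputs).** From the protocol: 18 per arm less 10% attrition, 18 × 0.9 = 16.2, so 16 per arm; two-sided 0.05. Assumed: a shift of 0.8 SD, the pre-post correlation r, and the share of patients at the ceiling at baseline. Compared are (a) Mann-Whitney on T1 − T0 and (b) rank ANCOVA, that is, ranked T1 regressed on group and ranked T0.

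Set-up 1: latent normal scores cut into 21 levels.

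| Ceiling at T0 | r | (a) change | (b) rank ANCOVA | Loss (points) |
|---|---|---|---|---|
| none | 0.5 | 0.536 | 0.670 | 13 |
| none | 0.7 | 0.747 | 0.799 | 5 |
| none | 0.85 | 0.96 | 0.95 | none |
| none | 0.9 | 0.99 | 0.99 | none |
| about 30% | 0.5 | 0.362 | 0.598 | 24 |
| about 30% | 0.7 | 0.488 | 0.693 | 21 |
| about 30% | 0.85 | 0.74 | 0.87 | 13 |

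With the 30% ceiling the loss shrinks to about 9 points near r = 0.9.

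Set-up 2: integer score 0 to 56, SD 5, control gain 1, effect 4 points (4 / 5 = 0.8 SD), with the baseline mean moved towards the top. Each cell shows (a) / (b).

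| Ceiling at T0 | r = 0.3 | r = 0.5 | r = 0.7 | r = 0.85 |
|---|---|---|---|---|
| about 0% | 0.421 / 0.584 | 0.556 / 0.667 | 0.768 / 0.810 | 0.967 / 0.962 |
| about 14% | 0.313 / 0.558 | 0.412 / 0.636 | 0.574 / 0.768 | 0.796 / 0.928 |
| about 38% | 0.196 / 0.462 | 0.235 / 0.508 | 0.330 / 0.626 | 0.437 / 0.749 |

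Method (a) is behind in 11 of the 12 cells, by 4 to 31 points, and level in the other.

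**Step 4: type I error.** With no group difference, rejection rates are about 4% to 6% for both methods in both set-ups.

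**Step 5: how often spacing matters.** Squaring the scores in set-up 1 changed the significance decision of (a) in 6% to 10% of trials at r = 0.5 and 0.7. Without a ceiling this falls to about 3% at r = 0.85 and 0.3% at r = 0.9. In set-up 2 (about 14% at ceiling, r = 0.7) the recoding −log(60 − score) changed it in 12.5% of trials. Mann-Whitney on the T1 score alone never changed.

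**Step 6: dropping the baseline is no remedy.** In set-up 2 without a ceiling at r = 0.7, Mann-Whitney on T1 alone has power 0.566, against 0.768 for change scores. The gain comes from adjusting for baseline, not from ignoring it.

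**The case against.** The strongest reply is that this is a choice between valid tests. Under randomisation, Mann-Whitney on change is a sound test of no treatment effect however the scale is numbered, and Step 4 confirms it. That stands. A reader might infer that the stated rule produces false positives; it does not.

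A reader might also infer that the primary result is compromised. The Functional Reach Test is measured in cm and reaches this route only if normality is rejected, and then the equal-interval argument does not apply. The affected scales are introduced as exploratory, in a trial that calls itself a pilot and a proof of concept. That stands too, and limits the weight of the point.

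A third inference would be that these patients sit near the top of their scales. Entry is restricted to Hoehn and Yahr stages II and III, which makes it plausible, but the protocol documents no ceiling for any scale. The ceiling figures are conditional.

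Two further replies carry some weight. Part of the loss without a ceiling is the general advantage of baseline adjustment over change scores and would arise for a continuous outcome too. Summing items into a score already accepts some numeric spacing, and because each scale's scoring is conventional, nobody would in practice recode it; the flips in Step 5 measure sensitivity, not analyst freedom. Neither reply gives a reason to prefer the stated test: the baseline is already collected, and the rank-adjusted analysis had higher or practically equal power in every setting tried.

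**Conclusion.** The point holds as one of interpretability and efficiency for the secondary outcomes treated as ordinal. That the ranks depend on spacing, and that patients at a scale limit are tied with non-improvers, follows from the stated rule alone. The power loss is usual but not universal: about 5 to 16 points at correlations of 0.3 to 0.7 without a ceiling, none at about 0.85 or above, and about 9 to 25 points with roughly 30% at the ceiling. These sizes rest on 16 completers per arm from the protocol and on an assumed 0.8 SD shift, correlation and ceiling share. Which scales are affected depends on which ones the trial classes as ordinal, and the protocol article does not say.

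**What to change.** For ordinal outcomes, replace Mann-Whitney on change scores with rank ANCOVA (Quade) of the follow-up score adjusted for the ranked T0 score, once at T1 and once at T2. If a proportional-odds model is preferred, enter baseline as ranks. With the raw baseline score as a numeric covariate, that model is itself sensitive to recoding: squaring the baseline changed its significance decision in 5% (r = 0.5) and 3.5% (r = 0.7) of 200 simulated trials.

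The cost is one sentence in the analysis section and slightly more analysis work, with no new data. The treatment effect is no longer expressed as a simple change, so medians by group and visit should be reported beside it. The second comparison then addresses status at twelve weeks given baseline, rather than change after T1, and the text should say so.

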c) *Posturographic outcome measures*: Tasks during posturographic evaluations consist of quiet stance and rhythmic tracking. Time series of the COP along anterio-posterior and mediolateral axes will be used to compute quantitative measures of task performance. In addition, stabilogram-analysis will be performed to investigate the dynamical and correlative structure of the data [36,37]. For quiet stance we will determine the COP’s variance, its temporal counterpart, the diffusion coefficient, as well as the scaling of the temporal correlation structure (the Hurst exponent). For rhythmic tracking we will follow the same approach but instead of the mere COP trajectory we will employ the distance between (the periodically moving) visual target and the COP in mediolateral direction (as displayed on the monitor). To specifically investigate effects on motor timing, we will also estimate the instantaneous relative phase between target and COP as well as the associated circular variance.

d) *EEG-related outcomes*: EEG will be recorded during the postural task. After artifact-removal based on independent component analysis [20], time-dependent EEG signals will undergo a conventional time-frequency analysis, followed by principal component analysis to identify significant changes in (frequency-dependent) motor-related potentials. We will further determine functional connectivity through neural synchronization in distinct frequency bands, i.e., the variance of the pair-wise relative phase between EEG signals. To localize the sources of brain activity we will combine the EEG signals with the co-registered anatomical MRIs and apply linearly constrained minimum variance beamformers [38,39]. Activities at the sources will finally be analyzed in the same form as the EEG signals at electrode level.

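### The Rayleigh test named for comparing arms on relative phase uniformity is a one-sample test and cannot test a difference between arms

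*Protocol article*

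**What the plan says.** The Statistical analysis section of the protocol article assigns relative phase to circular statistics, "using, in particular, Rayleigh tests to analyze group differences of relative phase uniformity between sources". Earlier in the same paragraph the ANOVA is given a "between-subjects factor *group* (experimental vs. control) and within-subjects factor *time* (T0, T1, and T2", so group there means trial arm. The significance rule is general: "P < 0.05 will be set (two-tailed) as threshold for significance".

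The next paragraph applies the same tools to the source-level EEG: "The (relative) phases of the source projected EEG activity in the beta frequency band will be assessed through circular statistics (see above"). Neither paragraph names a two-sample circular test.

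Under Secondary outcome measures, functional connectivity is defined as "the variance of the pair-wise relative phase between EEG signals". The posturographic outcomes there include the relative phase between target and centre of pressure, with its circular variance. The Background links these measures to a second hypothesis, that "VF-related changes in balance performance are associated with more pronounced (movement-related changes in) beta synchronization in primary motor areas".

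**The concern.** The null hypothesis of the Rayleigh test is that one set of angles is spread evenly round the circle. No parameter in it describes how two sets differ. Assigned to a group comparison, it can be used in two ways:

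- **Once per arm, comparing the verdicts.** One arm significant and the other not does not show that the arms differ, and both significant does not show that they agree.
- **Once on the pooled patients.** Rejection then shows phase locking in the whole sample and says nothing about treatment.

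Either way, a reported arm effect on phase uniformity would not rest on a test of that effect. False differences could be read as neurophysiological evidence for visual feedback training, and real ones could be missed.

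**Working it through.** **Figure in the plan.** The article gives no power, effect size or variance for relative phase, so there is no figure to reproduce. The check is of how the named test behaves when put to the stated use.

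**Inputs from the article.** Two arms, "an estimated attrition rate of 10%, we plan to include thirty-six patients in total, eighteen in each group". After 10% attrition, 18 × 0.9 = 16.2, or about 16 per arm. Two-sided threshold 0.05.

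**Assumptions, none of them stated in the article.** One angle per patient; von Mises phases with concentration kappa; a rule that calls the arms different when one is significant and the other is not. The mean resultant length is R = I₁(kappa)/I₀(kappa), where 0 is no locking and 1 is perfect locking.

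**Test.** For n angles with resultant sum S, the usual approximation is p = exp{√[1 + 4n + 4(n² − S²)] − (1 + 2n)}. Each setting used 20,000 simulated trials.

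**Step 1: identical arms, one test per arm.** If each arm rejects with probability q, the verdicts conflict with probability 2q(1 − q). For n = 18:

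| kappa | R | q per arm | 2q(1 − q) | Simulated conflict |
|---|---|---|---|---|
| 0 | 0 | 0.051 | 0.097 | 0.095 |
| 0.5 | 0.24 | 0.230 | 0.354 | 0.353 |
| 0.8 | 0.37 | 0.520 | 0.499 | 0.497 |
| 1.0 | 0.45 | 0.703 | 0.418 | 0.418 |
| 1.5 | 0.60 | 0.958 | 0.080 | 0.081 |
| 2.0 | 0.70 | 0.997 | 0.006 | 0.005 |

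The formula explains the shape. Conflict peaks at one half when each arm has even odds of rejecting, and vanishes when both arms almost always reject. At n = 16 the peak is also about 0.50, at kappa 0.8.

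**Step 2: arms that truly differ in locking.** For R = 0.50 versus 0.80 (kappa 1.16 versus 2.87, n = 18), the weaker arm rejects in about 82% of trials and the stronger in practically all. Both are significant in about 0.82 × 1.00 = 82%, so the rule shows a difference in only about 18%. For kappa 2 versus 10 it shows one in 0.3%.

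**Step 3: arms that differ in mean phase.** With kappa 3 in both arms and mean phases 90 degrees apart, the verdicts conflict in 0.0% of trials.

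**Step 4: one pooled test on identical arms (n = 36).** It rejects in 44%, 96% and 100% of trials at kappa 0.5, 1.0 and 2.0, although there is no arm difference.

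**Step 5: a direct two-arm comparison.** A group-label permutation test on the difference in mean resultant length (600 trials, 300 permutations each, n = 18) rejected for identical arms in 5.2% (kappa 0.7) and 6.8% (kappa 1.0). The simulation standard error is √(0.05 × 0.95/600) = 0.9 points, so the second figure is about two standard errors above nominal. Power for kappa 2 versus 10 was about 90%, against 0.3% in Step 2. This comparator also uses one angle per patient. It shows what a direct test can do, and is not a power estimate for the per-patient measure recommended under the fix.

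**The case against.** Several objections limit the point.

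- **A between-arm route already exists.** A reader might infer that the plan has no way to compare arms on synchronization. The article does not support that. Circular variance and the variance of relative phase can be computed as one continuous value per patient and visit. The same section sends continuous outcomes measured at all three time points to the group-by-time ANOVA, or to Mann–Whitney tests on change scores. This stands: the fault is one misassigned test.
- **The wording is not exhaustive.** The sentence says only that Rayleigh tests are used in particular, and it leans on cited methods papers that are not available here. They may contain a valid two-sample step. That rules out claiming that none is intended, but the article still gives the Rayleigh test a purpose it cannot serve.
- **The beamformer check is not a fault.** A reader might see a second missing arm comparison where sources are "tested for within-group consistency through permutation tests". That step locates sources, and a within-group check is reasonable there.
- **The hypothesis is partly about association.** The Background ties synchronization to changes in balance performance, and the plan compares correlation coefficients for that. It should not be read as a purely between-arm claim.
- **The percentages are conditional.** The article states neither the compare-verdicts rule nor one angle per patient, and the concentrations are illustrative. This stands, so the full range is shown.

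**Conclusion.** The point holds in narrow form: a one-sample uniformity test is named for a between-arm question, and no reading of the Rayleigh test itself makes it answer that question. This follows from the definition of the test and needs no simulation.

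The practical size depends on the assumptions listed in the working. Under them, identical arms give conflicting verdicts in anywhere from about 0% to 50% of trials, and a true difference of 0.50 versus 0.80 is hidden in about 82%. These figures illustrate an inferred procedure and are not the trial's false-positive rate or power.

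The affected outcomes are secondary and exploratory, in a trial that describes itself as a pilot and a proof of concept. The Functional Reach Test, its sample size and its analysis are untouched. Severity is moderate.

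**What to change.** Reword the sentence in the Statistical analysis section, before any data are analysed by arm, so that:

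1. Rayleigh tests describe phase locking within an arm only.
2. Arms are compared on per-patient phase-locking strength, defined as 1 minus the circular variance of relative phase. The comparison uses the T1 value adjusted for T0, or the change from T0, by a group-label permutation test or the planned ANOVA/Mann–Whitney route. One of these should be chosen in advance.
3. If mean phase direction is of interest, a two-sample circular test such as Watson U² or Watson–Williams is named for it.
4. The cross-reference for source-level beta-band phases points to the revised text.

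The source-consistency permutation test needs no change. The cost is a few sentences and a few lines of code, with no new data, visits or patients.
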